##### Outcome measures (intervention effectiveness)

Primary outcome

The primary outcome is exhaustion (intervention effectiveness). Change from baseline in self-reported exhaustion during 6-, 12-, 18- and 24-months follow-up is assessed by the same questionnaire as described above. We hypothesise that adherence to the recommendations of the guideline will reduce self-reported exhaustion assessed with the exhaustion scale of the Oldenburg Burnout Inventory (OLBI) [51]. Six items of the inventory are used with answering categories ranging from (1) “strongly agree” to (4) “strongly disagree”.

Secondary outcomes

The following secondary outcomes are assessed at baseline and at 6, 12, 18 and 24 months with the same questionnaire as described under implementation effectiveness directed at the school-management and school-personnel. Long-term sick-leave is assessed by register-data from the Swedish Social Insurance Agency. An overview of each secondary outcome and a description of the items used is given below.

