### Objectives

The primary objective of this study is to compare the effectiveness of a multifaceted implementation strategy versus a single implementation strategy for implementing the *Guideline for the prevention of mental ill-health at the workplace* within schools. The effectiveness will be compared with regard to the extent to which the recommendations are implemented within the schools (implementation effectiveness) and with regard to social and organisational risk factors for mental ill-health, absenteeism and presenteeism (intervention effectiveness).

The hypothesis is that schools that receive support in implementing the guideline through a multifaceted implementation strategy are more responsive to working in a structured and systematic manner with the management of social and organisational risks at their workplace and consequently reduce risk factors for mental ill-health, compared to schools that receive support through a single implementation strategy based on education.

The secondary objective is to evaluate the implementation process of the guideline within schools. This will be done by collecting qualitative and quantitative data on implementation outcomes as defined by Proctor and colleagues [35]. Moreover, contextual factors (barriers and facilitating factors) that may influence the implementation process will be identified. This is done by collecting qualitative and quantitative data on barriers and facilitators in accordance with the CFIR [21]. This will give a better understanding of factors that may influence the process and will inform future necessary adaptation of the implementation strategies.

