### Trial design

The study is a 12-month cluster-randomized waiting list-controlled trial with before and after measurements involving 20 primary schools in two municipalities in Sweden. Randomization (1:1 allocation to intervention and waiting list control) is conducted at the school level. Primary schools are randomized by a computer-generated randomization-list to either the ARM 1 or ARM 2 after stratification in blocks by municipality and school size (number of students per school). Schools in ARM 1 will receive all three implementation strategies during the first year of the study period while schools in ARM 2 will receive only the educational strategy in year 1 and continue with the other strategies during year 2 (Fig. 2). The implementation strategies target the managerial level of first line managers i.e. school-principals. All employees of the participating schools will be invited to complete outcome-questionnaires at baseline and 6-, 12-, 18- and 24-months follow-up during working hours.

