### Sickness absence

Change in self-report baseline short-term sick leave (last 7-days) during 6-, 12-, 18- and 24-months follow-up is assessed with two items [45]. One item assesses the number of hours worked per week; the other item assesses how many days in the last 7 days the respondent has been away from work due to sickness. Change in long-term sick leave is assessed by register-data from the Swedish Social Insurance Agency. Information is collected on long-term sick leave (> 2 weeks) due to mental ill-health (F diagnoses according to ICD-10 (International Statistical Classification of Diseases and Related Health Problems). Data is collected for the entire study period (24 months) and 1 year prior to baseline. Only data on sick leave related to depression, anxiety, or stress problems (light form of mental illness) is collected. Employees provide a separate written consent for the collection of their personal sickness data from the Swedish Social Insurance Agency.

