#### Statistical methods

The hypothesis is that the participants in ARM 1 when compared to the participants in ARM 2 will demonstrate improvements in exhaustion over time, as their schools will demonstrate higher adherence to the recommendations of the guideline compared to schools in the control group. Secondary hypotheses are that ARM 1 participants when compared to ARM 2 participants will demonstrate significant improvements in experience of job-demands, work organisation and job contents, interpersonal relations and leadership, presenteeism, work performance, recovery, work-life balance, work engagement, self-perceived stress, self-rated health, sickness absence and psychosocial safety climate.

Intention-to-treat analyses will be performed and where relevant, compared to per-protocol analyses. The aim of the statistical analyses is to examine the between group differences over time in adherence to the recommendations of the guideline (implementation effectiveness) and in exhaustion and the other individual level outcomes. The outcome variable adherence to the recommendations of the guideline will be operationalized into level of adherence based on the questionnaire developed by the research team. We will use mixed effects regression models to test the hypotheses of between groups difference in exhaustion. This analysis will allow for the modelling of data on school personnel, nested within the schools. Moreover, mixed models structure allows for inter-personnel and inter-schools heterogeneity through random effects such as individual intercepts and slopes over time. If potential confounders are unevenly distributed and if this is likely to affect the results when the two arms are compared, these factors will be adjusted for in the analyses. Possible interaction effects on the outcomes will be checked for. If they are statistically significant, stratified analyses will be considered. Finally, exploratory analysis will be performed to compare schools with high adherence to the recommendations of the guidelines compared to schools with low adherence. These analyses will for example examine differential effects on exhaustion and secondary outcomes. In addition, we will examine potential moderators such as school size, stability in school management etc. A detailed statistical analysis plan will be developed in collaboration with a statistician prior to starting the data analysis.

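### The primary outcome spans 6 to 24 months with no primary wave, although the multifaceted-versus-single contrast exists only through month 12

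*Protocol article*

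**What the plan says.** All places are in the protocol article.

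- **Question.** The primary objective (Objectives) is to "compare the effectiveness of a multifaceted implementation strategy versus a single implementation strategy".
- **Exposure by year.** Trial design states: "Schools in ARM 1 will receive all three implementation strategies during the first year of the study period". For the comparator, "schools in ARM 2 will receive only the educational strategy in year 1 and continue with the other strategies during year 2".
- **Label.** The same section says: "The study is a 12-month cluster-randomized waiting list-controlled trial with before and after measurements". It also schedules questionnaires to 24 months.
- **Primary outcome.** Outcome measures (intervention effectiveness) gives it as "Change from baseline in self-reported exhaustion during 6-, 12-, 18- and 24-months follow-up", measured by questionnaire. No wave is singled out.
- **Analysis.** Statistical methods says: "The aim of the statistical analyses is to examine the between group differences over time in adherence", and the sentence goes on to cover exhaustion and the other individual-level outcomes. It names mixed-effects regression with random effects for people and schools. It gives no end of window and no form for the fixed effect of time. A detailed analysis plan is to follow before analysis starts.
- **Sample size.** The 30% improvement in exhaustion has no time point.
- **Other outcomes.** Adherence and the questionnaire-based secondary outcomes use the same four follow-ups. For register sick leave, "Data is collected for the entire study period (24 months) and 1 year prior to baseline". Text-message stress is limited to 12 months.

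**The concern.** Randomisation supports the stated question only while the arms receive different things. From the start of year 2, ARM 2 is given the components that define the multifaceted arm. At 18 and 24 months the randomised comparison is still valid, but it answers a different question: early against delayed multifaceted support.

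The stated primary outcome treats all four follow-ups alike. An analyst who follows it literally brings two post-crossover waves into the primary comparison. If ARM 2 benefits from its delayed support, the estimated difference shrinks, and a strategy that works could look ineffective. With no wave named in the outcome definition, the hypothesis or the sample size, the choice among four waves is also left open.

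**Working it through.** **1. When the contrast exists** (T0 to T4 are months 0, 6, 12, 18 and 24)

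| Wave | ARM 1 | ARM 2 | Comparison |
|---|---|---|---|
| T1, T2 | all three strategies | education only | multifaceted vs single |
| T3, T4 | all three, from year 1 | education in year 1, other strategies in year 2 | early vs delayed multifaceted |

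**2. Dilution, free of SD, ICC and sample size.** Let δ be the effect after a year of delivery. Assume it builds linearly over each arm's delivery year and then holds, with full catch-up by ARM 2. The arm differences at T0 to T4 are 0, 0.5δ, δ, 0.5δ, 0.

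- Mean over T1–T4: (0.5 + 1 + 0.5 + 0)δ / 4 = 0.5δ.
- Least-squares slope on month, centred at 12: numerator (−12)(0) + (−6)(0.5δ) + 0(δ) + 6(0.5δ) + 12(0) = 0, so the slope is 0.

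If instead the effect is immediate and ARM 2 has caught up by month 18 (0, δ, δ, 0, 0), the mean is again 0.5δ. The slope is (−6δ)/360 per month, slightly in the wrong direction. With half catch-up at T3 and T4 (0, δ, δ, 0.5δ, 0.5δ), the mean is 3δ/4 = 0.75δ. With no catch-up the mean stays at δ.

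**3. The plan's sample size.** Inputs from the Sample size section: 80% power, 0.05 level (two-sided assumed), ICC 0.005, about 400 people, at least 18 schools. No SD, baseline mean or baseline rate is given, so the figure cannot be reproduced from the plan's inputs alone. Reading 30% as 0.30 SD:

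- n per arm = 2(1.960 + 0.842)² / 0.30² = 174.4, rounded up to 175.
- Mean cluster size 400/18 = 22.2; design effect 1 + 21.2 × 0.005 = 1.106.
- 175 × 1.106 = 193.6, rounded up to 194 per arm, 388 in total. This is within 3% of 400.

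Other readings are possible. A 30% relative fall in a proportion needs 378 people at a 50% baseline and 812 at 30%. The 0.30 SD is therefore an assumption.

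**4. Power under that assumption.** Effective n per arm = 200/1.106 = 180.8. Power = Φ(d√(180.8/2) − 1.96) = Φ(9.508d − 1.96).

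- T2 alone, d = 0.30: Φ(0.892) = 81%.
- T1–T4 average, full catch-up, d = 0.15, no precision gain from averaging: Φ(−0.534) = 30%.
- T1–T4 average, half catch-up, d = 0.225, no precision gain: Φ(0.179) = 57%.

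Averaging four correlated waves reduces the SD by the factor √((1 + 3r)/4), where r is the within-person correlation (assumed, same design effect):

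| r | SD factor | Power, full catch-up | Power, half catch-up |
|---|---|---|---|
| 0.8 | 0.922 | 34% | 64% |
| 0.6 | 0.837 | 40% | 73% |
| 0.4 | 0.742 | 49% | 82% |

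At half catch-up with r = 0.4 the precision gain offsets the lost power, but the estimate is still 0.75δ rather than δ.

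**The case against.** The strongest case on the other side is that the article specifies neither a pooled nor a linear-trend test. The outcome sentence can be read as a list of measurement waves. The slopes in Statistical methods are random effects describing variation between people and schools, not a fixed arm-by-time term. With categorical time, the T1 and T2 contrasts are untouched by later waves. A 12-month controlled phase followed by measurement while the waiting-list arm is treated is a coherent design, and the 12-month label points that way. Details of time coding commonly belong in an analysis plan, which is promised and not shown.

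Much of this stands. A reader might infer that the planned analysis will cancel the effect. The documents do not support that, because no such analysis is fixed. A reader might also infer that every secondary outcome is affected, but text-message stress already stops at 12 months. Nor is there evidence that T2 collection overlaps ARM 2's later delivery, so no condition on its timing follows.

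The objection does not remove the point. The window of the primary outcome is not left open for later: the article states it as four follow-ups, two of them after ARM 2's planned change. The 12-month label is not carried into the outcome, hypothesis, sample size or analysis text. An analysis plan limited to year 1 would be narrowing the published primary outcome, so the outcome text itself needs correction.

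**Conclusion.** The point holds as a badly fixed primary comparison. The multifaceted-versus-single contrast ends at month 12, the stated primary outcome runs to month 24, and nothing beyond a label directs the analyst to year 1.

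The harm is conditional on an analysis that pools T3 and T4 or fits a common trend. It then depends on how far ARM 2 catches up: the four-wave average is half the 12-month effect with full catch-up, three quarters with half catch-up, and undiluted with none. The zero slope needs the gradual build-up and full catch-up described above. The power figures rest further on 0.30 SD, a two-sided test and a constant design effect. They are illustrations, not predictions for this trial.

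**What to change.** 1. Name the ARM 1 minus ARM 2 difference in exhaustion at 12 months (T2) as the primary comparison, estimated from a mixed model with categorical time. Treat T1 as secondary.
2. Apply the same year-1 window to the between-arm comparisons of adherence, the questionnaire-based secondary outcomes and register sick leave. Text-message stress needs no change.
3. Report T3 and T4 as maintenance in ARM 1, before-after change in ARM 2, or early versus delayed delivery, and keep them out of the primary randomised contrast.
4. Tie the sample-size statement to 12 months.

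This changes wording in the protocol and analysis plan. It needs no new data and no change to delivery or collection. The cost is that T3 and T4 no longer contribute to the primary test, which gives up some precision if ARM 2 in fact catches up little.

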### Demands at work

Change from baseline in self-reported demands at work during 6-, 12-, 18- and 24- months follow-up is assessed with the Copenhagen Psychosocial Questionnaire (COPSOQ) II [42]. The COPSOQ II is a well-established instrument aimed at assessing the psychosocial work environment. COPSOQ has been widely used to assess teacher’s psychosocial work environment [39]. Three different types of demands at work are assessed: quantitative demands, work pace and emotional demands. Quantitative demands (e.g. Do you get behind with your work?) are assessed with four items, work pace is assessed with three items (e.g. Do you have to work very fast?) and emotional demands (e.g. Is your work emotionally demanding) are assessed with four items. All items have 5-point response anchors ranging from (1) “always” to (5) “never/hardly ever”.

### Work organization and job contents

Eleven items of the COPSOQ II are used to assess three domains of work organisation and job contents, namely influence at work, possibilities for development and commitment to the workplace. All items have 5-point response anchors ranging from (1) “always” to (5) “never/hardly ever”*.* Change from baseline in self-reported influence at work (e.g. Do you have a say in choosing who you work with?) during 6-, 12-, 18- and 24-months follow-up is assessed with four items. Change from baseline in self-reported possibilities for development (e.g. Can you use your skills or expertise in your work?) during 6-, 12-, 18- and 24-months follow-up is assessed with four items. Change from baseline in self-reported commitment to the workplace (e.g. how often do you consider changing jobs?) during 6-, 12-, 18- and 24-months follow-up is assessed with three items.

### Interpersonal relations and leadership

Nine items of the COPSOQ II are used to assess three domains, namely social support from superior, social support from colleagues and recognition by management. Change from baseline social support from superior (e.g. How often do you talk with your superior about how well you carry out your work?) during 6-, 12-, 18- and 24- months follow-up is assessed with three items with 5-point response anchors ranging from (1) “always” to (5) “never/ never/hardly ever”. Change from baseline social support from colleagues (e.g. How often do you talk with your colleagues about how well you carry out your work?) during 6-, 12-, 18- and 24-months follow-up is assessed with three items with 5-point response anchors ranging from (1) “always” to (5) “never/hardly ever”. Change from baseline recognition by management (e.g. Is your work recognised and appreciated by the management?) during 6-, 12-, 18- and 24-months follow-up is assessed with three items with 5-point response anchors ranging from (1) “to a very large extend” to (5) “to a very small extend”.

### Presenteeism

Change in baseline presenteeism during 6-, 12-, 18- and 24-months follow-up is assessed with a single item developed and validated by Aronsson and colleagues [43]. Presenteeism is defined as coming to work despite health problems with answering categories “yes” or “no”.

### Work performance

Change in baseline work performance during 6-, 12-, 18- and 24-months follow-up is assessed by using a modified version of the *Work Productivity and Impairment Scale General Health Questionnaire* (*WPAI: GH* [44, 45]*).* The questions concern the extent to which the individual experiences that their work performance is affected by health problems and the extent to which the individual experiences that their work performance is affected by work-related problems. The response anchors range from “health problems/work-related problems have not influenced my work” (0) to “health problems/work-related problems have completely prevented me from working” (10).

### Recovery

Change in baseline recovery during 6-, 12-, 18- and 24-months follow-up is assessed with a single item [46] with 5-point response anchors ranging from (1) “never” to (5) “very often”.

### Work-life balance

Change in baseline work-life balance (e.g. my work drains so much of my energy that it has a negative effect on my private life) during 6-, 12-, 18- and 24- months follow-up is assessed with 4-items of the COPSOQ with 4-point response anchors ranging from (1) “yes, definitely” to (4) “no, not at all”.

### Work engagement

Change in baseline work engagement during 6-, 12-, 18- and 24-months follow-up is assessed with the three statements of the Utrecht Work Engagement Scale (UWES) [47] with six response anchors ranging from (0) never to (5) always, every day.

### Self-reported stress

Change in self-reported stress during 6-, 12-, 18- and 24-months follow-up is assessed with a single question [48] with five response anchors ranging from (1) “not at all” (5) “very much”. In addition to assessing change in baseline self-reported stress by questionnaire we will also assess stress by sending a validated question by text message by mobile phone with SMS-track (https://sms-track.com/) every 4th week over 12 months. This question has been used in our previous studies on stress prevention in the workplace and involves sending a Short Message Service (SMS) every week over 12 months with a high response rate and gives a good indication of changes in stress over time [49].

### Self-perceived health

Change in baseline self-perceived health during 6-, 12-, 18- and 24- months follow-up is assessed with a single question from the SF-12 Health Survey (Short-Form Health Survey [50] with 5-point response anchors ranging from (1) excellent to (5) bad.

### Sickness absence

Change in self-report baseline short-term sick leave (last 7-days) during 6-, 12-, 18- and 24-months follow-up is assessed with two items [45]. One item assesses the number of hours worked per week; the other item assesses how many days in the last 7 days the respondent has been away from work due to sickness. Change in long-term sick leave is assessed by register-data from the Swedish Social Insurance Agency. Information is collected on long-term sick leave (> 2 weeks) due to mental ill-health (F diagnoses according to ICD-10 (International Statistical Classification of Diseases and Related Health Problems). Data is collected for the entire study period (24 months) and 1 year prior to baseline. Only data on sick leave related to depression, anxiety, or stress problems (light form of mental illness) is collected. Employees provide a separate written consent for the collection of their personal sickness data from the Swedish Social Insurance Agency.

### Psychosocial safety climate

Change in baseline self-reported psychosocial safety climate (PSC) during 6-, 12-, 18- and 24-months follow-up is assessed with 12 items of the Psychosocial Safety Climate Scale [52] with 5-point response anchors ranging from (1) strongly disagree to (5) strongly agree. For example, my workplace management acts quickly to correct problems/issues that contribute to employees’ psychosocial health. The items measure the concept of psychosocial safety climate, which refers to an organizational climate for psychological health, wellbeing and safety and reflects the extent to which the senior management, according to the employees, commits to stress prevention at work [52].

#### Process evaluation

The implementation process of the educational meeting, implementation team and workshops are evaluated to investigate how well they have been implemented by collecting information on implementation outcomes as defined by Proctor and colleagues [35]. Implementation outcomes include reach, acceptability, satisfaction, feasibility, and fidelity. In addition, barriers and facilitators are assessed by interviews.

#### Reach

Reach is operationalized as the absolute number and proportion of individuals who participate in the educational meeting and workshop series. Reach is assessed through attendance lists, which are completed by the research team during the educational meetings and during each workshop.

#### Acceptability and satisfaction

Acceptability of the educational meeting and workshops is operationalized as the perception of the participants that the meeting and workshops are agreeable and satisfactory. Acceptability is assessed by questionnaire, which is completed directly after the educational meeting and after each workshop. The questionnaire includes 12 statements regarding the educational meeting/workshop structure and contents, with 5-point answering anchors ranging from (1) “to a very small extent” to (5) “to a very large extent” (e.g. The content of the meeting/workshop was relevant for implementing the recommendations of the guideline). In addition, the participants are asked to provide an overall rating for the educational meeting and workshops on a scale from 1 to 10 and to describe if any parts of the educational meeting or workshops need improving and which parts are good.

After the end of the implementation strategies, semi-structured interviews with implementation team members are performed to explore their views on the acceptability of the implementation strategies (i.e. educational meeting, implementation team and workshop series).

